### Objectives {7}

The primary objective of the present study is to determine if different exercise types produce varied outputs on CPM in a subgroup of CLBP patients classified as having CS pain. The secondary objectives are to evaluate if a 12-week exercise intervention program would alter executive functioning, QoL, disability, and pain and to examine the relationship between patient characteristics, executive functions, CPM, and QoL in CLBP patients.

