### Trial design {8}

This is a randomized, controlled, double-blinded study determining how CPM changes in response to three types of active exercises in CS-positive CLBP patients. Participants will be randomized to undergo 12 weeks of the motor control exercise (MCE), superficial strengthening (SS), or AE combined with patient education or patient education alone. This active treatment concurrent control design will be used to demonstrate superiority of one exercise group over another. All patients will be allocated in a 1:1:1:1 ratio using random number tables. All participants will receive advice to stay active. Another no-pain control group will also be recruited. The intervention will be provided for 12 weeks. An independent assessor will collect data at baseline (t0), after intervention at 3 months (t1), and at the 6-month follow-up (t2). Outcome measures include CPT for measuring CPM, letter–number sequencing subtest in the Wechsler Adult Intelligence Scale-III Edition (WAIS-III), Stroop neurophysiological test, QoL assessed using the abbreviated WHOQOL-BREF questionnaire, isometric muscle strength of spine and hip muscles, the Oswestry Disability Index (ODI) questionnaire, and the Numerical Pain Rating Scale (NPRS). Table 1 and Fig. 1 present the study design and flowchart, respectively. The research ethics approval was granted by the Integral University, India (IIAHSR/DO/PT/2022/23), and Composite Regional Centre for Skill Development, Rehabilitation, and Empowerment of Persons with Disabilities, India (CRCL/Ph.D. Data Collection/2021–22/1556). The study is designed according to the Consolidated Standards of Reporting Trials (CONSORT) guidelines and reported according to the Standard Protocol Items: Recommendations for Interventional Trials (SPIRIT) checklist. The study will use a 5 (between subjects − type of exercise interventions: MCE vs. AE vs. SS vs. patient education vs. no-pain control) × 3 (within subjects − time: before vs. after vs. 3 months after the intervention) mixed design.

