### Interventions

#### Explanation for the choice of comparators {6b}

The control group populations comprising the no-pain population and CS-positive patients with CLBP will help determine the effectiveness of interventions and allow us to gather valuable information for a better understanding of the impact of endogenous analgesia on pain control. The choice of a comparator is further strengthened by the results of recent recommendations that clinicians should employ standard education strategies, including exercise and physical activity, for CLBP patients [30].

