#### Intervention description {11a}

All patients who report for CLBP management will be continuously enrolled in the study. They will undergo a standardized history taking for recording of their demographic details and will be screened for eligibility. The first author will conduct a complete physical assessment and neurological examination, and the presence of “red flags” will be closely monitored. The patients providing voluntary informed consent will be referred to the outpatient departments (OPDs) of the concerned study center where more detailed evaluations will be conducted.

In case of any doubt about a participant’s capacity to engage in the exercise program, they will be directed to a medical professional for an evaluation. The same process will continue until all participants have been recruited (*n* = 172). The recruited participants will then be randomized to receive one of the three exercise interventions along with patient education or patient education alone. A group comprising healthy volunteers will serve as the control group. The interventions will last for 12 weeks. Follow-up will be conducted 3 and 6 months after the intervention.

Three qualified physiotherapists (PTs) in each center will provide the interventions. All of them have a postgraduate degree in musculoskeletal physiotherapy and an average of 11 years of clinical experience. Before initiation of the study, they will attend a training session discussing the detailed treatment procedures. All PTs will be instructed to adhere to the treatment checklist provided and to complete treatment notes after each session. The participants will be instructed to avoid engaging in any other physical program during the study period and to not exercise at home during the intervention period. All the three participant groups will receive the targeted exercise interventions along with the same health education provided to group 4 participants. In order to manage time as effectively as possible, every exercise group will have 5–7 participants. The participants will be advised to continue the exercises after the treatments are over in order to support self-management.

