### Statistical methods

#### Statistical methods for primary and secondary outcomes {20a,b}

The Shapiro–Wilk test will be used to assess the normality of the distribution of the data. A one-way analysis of variance (ANOVA) will be used to compare baseline characteristics between the groups. Descriptive statistics will be used to calculate the mean values of all outcome variables collected. A repeated measure ANOVA statistic will be used to evaluate the effect of three types of exercise interventions on CPM, neurophysiological outcomes, pain, disability, strength measures, and QoL. The study will use a 5 (between subjects – type of exercise interventions: AE vs. MCE vs. SS vs. patient education vs. no-pain control) × 3 (within subjects – time: before vs. after vs. 3 months after the intervention) mixed design. Tukey’s post hoc analysis will be conducted to establish differences between the groups. Effect size will be estimated by dividing the mean difference in outcomes between the intervention and control groups by the combined standard deviation of the two groups [56].

The primary outcome will undergo a per-protocol analysis. Pearson correlation analysis will be performed to determine the relationship between patient characteristics (Table 4), CPM, executive functioning, pain, strength measures, disability, and QoL. Multiple linear regression analysis will be used to deduce the characteristics of individuals responding positively to exercise interventions. For all measurements, *p* will be considered significant, if it is < 0.05. The data collected will be analyzed using SPSS (Statistical Program for the Social Sciences) 16.0 (IBM Corp., Armonk, NY).

**Table 4 Tab4:** Summary of patient characteristics to be collected

Characteristics	CLBP group	Control group
Age (years)	X	X
Gender (male/female)	X	X
Pain episode duration (weeks)	X	X
Body mass index (kg/m^2^)	X	X
Education level (yes/no; school incomplete, completed secondary school, completed diploma/completed bachelors and above)	X	X
Employment status (yes/no; employed (full or part-time), unemployed, retired)	X	X
Marital status (yes/no; married/separated/ divorced, single)	X	X
Personal behaviors Alcohol status (yes/no) Smoking status (yes/no)	X	X
Comorbidities	X	X
Fear avoidance behavior	X	X
Perception of improvement	X	X

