### Study limitations

Limiting the study to CS-positive participants will limit the generalization of the results. Long-term effects of exercises on CPM will not be evaluated, and the results may not be applicable to the older population. The role of confounding factors such as gender, body mass index, and level of physical activities will not be considered in this study. Future studies should evaluate the role of potential confounders associated with the CPM response.

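### The no-pain volunteers are entered as a fifth level of the intervention factor, so the omnibus ANOVA tests do not test the primary objective, which concerns only the four randomised patient arms

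*Protocol article*

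**What the plan says.** The protocol article's primary objective (Objectives {7}) is to "determine if different exercise types produce varied outputs on CPM in a subgroup of CLBP patients classified as having CS pain". Randomisation covers patients only. Trial design {8} states: "All patients will be allocated in a 1:1:1:1 ratio using random number tables". Intervention description {11a} adds: "The recruited participants will then be randomized to receive one of the three exercise interventions along with patient education or patient education alone". The fifth group is recruited separately (Study setting {9}, 43 people), and no exercise or education programme is described for it: "A group comprising healthy volunteers will serve as the control group".

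Statistical methods {20a,b} then specifies a repeated-measures ANOVA that "will be used to evaluate the effect of three types of exercise interventions on CPM, neurophysiological outcomes, pain, disability, strength measures, and QoL". Its between-subject factor is "type of exercise interventions: AE vs. MCE vs. SS vs. patient education vs. no-pain control", crossed with three time points. Trial design {8} gives the same 5 × 3 layout. Tukey's test follows, with no restriction on which pairs it covers. No group or group-by-time test confined to the randomised arms is stated.

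Explanation for the choice of comparators {6b} presents the healthy group as evidence on efficacy: "The control group populations comprising the no-pain population and CS-positive patients with CLBP will help determine the effectiveness of interventions".

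**The concern.** An omnibus F test asks whether any of its groups differ. Once healthy volunteers are one of five levels, the group test can be driven by patients differing from healthy people. The group-by-time test can be driven by all patients changing together while the volunteers do not. Neither pattern says anything about whether aerobic, motor control and strengthening exercise differ, which is the stated objective.

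Because the factor is labelled as type of exercise intervention, a significant omnibus result invites exactly that reading. The wording in {6b} reinforces it. A further cost is that Tukey's test must cover ten pairs instead of six, which makes each comparison among patient arms harder to detect.

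**Working it through.** **The plan's own figure.** Sample size {14} gives SD 100 kPa, difference 80 kPa, 30 per group, two-sided 5% and 87% power. The noncentrality is 0.8/√(2/30) = 3.098. The normal approximation gives 87.3% and the noncentral t 86.1%, so the figure reproduces. 30/0.70 = 42.9, hence 43 per group, and 4 × 43 = 172 patients.

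**Assumptions that are not in the protocol.** Between-visit correlation ρ is 0.3, 0.5 or 0.7, equal for all pairs of visits. The four patient arms are identical. The patient–healthy offset δ is constant over the three visits. The common change c in all patients is present at both post-baseline visits and absent in the no-pain group.

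**Group test, five levels (4 and 145 df).** The variance of a person's mean over three visits is σ²(1+2ρ)/3. One group of five offset by δ gives

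λ = n·δ²·(4/5) / [σ²(1+2ρ)/3].

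For n = 30, δ = 80 and ρ = 0.5: λ = 30 × 0.64 × 0.8 / 0.667 = 23.04.

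**Group-by-time test, five levels (8 and 290 df).** The time pattern (0, 1, 1), centred, has sum of squares 2/3, so

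λ = n·c²·(4/5)·(2/3) / [σ²(1−ρ)].

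For n = 30, c = 40 and ρ = 0.5: λ = 30 × 0.16 × 0.8 × 0.667 / 0.5 = 5.12.

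Rejection rates at n = 30, from the noncentral F:

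| Situation with identical patient arms | ρ = 0.3 | ρ = 0.5 | ρ = 0.7 |
|---|---|---|---|
| Group test, offset 20 kPa | 15% | 13% | 12% |
| Group test, offset 30 kPa | 31% | 25% | 22% |
| Group test, offset 80 kPa | 99.5% | 97.9% | 95.0% |
| Group × time, common change 40 kPa | 21.3% | 29.6% | 49.5% |
| Group × time, common change 60 kPa | 47.7% | 64.9% | 89.3% |

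Simulation of the 5 × 3 ANOVA agrees to within about one percentage point: 13–26% for 20–30 kPa at ρ = 0.5, 96–99.7% for 80 kPa, and 22–49% and 48–89% for the two common changes. In simulations restricted to the four randomised arms, both tests rejected in about 4 to 6% of trials. A constant offset moves only the group test; group-by-time stays near 5%.

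**Tukey power for one 80 kPa difference.** The critical value on the t scale is the studentised range divided by √2.

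| n per group | Four groups | Five groups |
|---|---|---|
| 30 (noncentrality 3.098) | 2.607, power 69% | 2.762, power 63% |
| 43 (noncentrality 3.709) | 2.595, power 87% | 2.752, power 83% |

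**Tukey error among the four identical arms, using the five-group critical value (n = 30).** With equal SDs, the chance of falsely separating any two patient arms is about 3.3%. If the no-pain SD is half the patients', it is about 5.8%. At one tenth, the pooled variance is (4 + 0.01)/5 = 0.802 of the patients' and the error is about 6.9%. A small no-pain SD is plausible where pain-free people sit near the floor, as on the NPRS or ODI.

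**The case against.** The strongest reply is that the plan does not use the omnibus test to locate differences. It uses Tukey's test for that, and Tukey's test over five groups falsely separates patient arms in only about 3% of trials with equal variances. This stands. A reader might infer that the plan will declare exercise types different when they are not; the planned post hoc step does not support that. A reader might also compute that an unadjusted 5% contrast, with one of five variances near zero, runs at 2(1 − Φ(1.96√0.8)) = 8%. The plan uses no such contrast.

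The inputs can also be challenged. The 80 kPa in Sample size {14} is the difference to be detected, not a patient–healthy gap, and Background and rationale {6a} reports mixed evidence on whether CPM is altered in these patients. Hence the 20 to 30 kPa rows. Entry selects on NPRS, not on CPM, so regression to the mean does not by itself supply a common CPM change.

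A further tempting step is to add a confounding charge from Study limitations: "The role of confounding factors such as gender, body mass index, and level of physical activities will not be considered in this study". The objectives contain no aim of attributing a CPM difference to pain status, and randomisation deals with confounding among the four arms, so this does not count against the efficacy analysis. Nor can the volunteers firmly be called untreated. No programme is described for them, but Trial design {8} says all participants receive advice to stay active.

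**Conclusion.** The factor is wrong as written. The five-level group and group-by-time tests do not test the primary objective, and they can reject well above 5% with no difference between patient arms. How far above depends on the assumed offset, common change and correlation: from about 13% at a 20 kPa offset (correlation 0.5) to over 95% at 80 kPa for the group test, and about 21 to 89% for group-by-time at common changes of 40 to 60 kPa.

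The damage is limited to the omnibus tests and their interpretation, plus a modest loss of Tukey power (six percentage points at n = 30, four at n = 43). Pairwise comparisons among patient arms remain usable. Their familywise error is about 3% with equal variances and reaches about 7% only if the no-pain SD is very small.

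**What to change.** - In Statistical methods {20a,b}, run the group and group-by-time efficacy tests and Tukey's test on the four randomised arms only.
- Remove the no-pain control from the intervention factor there and in Trial design {8}, so that the efficacy design becomes 4 × 3.
- Report the no-pain group at all three time points as a separate reference comparison, adjusted if wished for age, sex and BMI, which Table 4 already collects in both groups. Confining this group to baseline would discard follow-up measurements that the design includes and that may serve as a reference for retest effects on the cognitive tests.
- Reword {6b} so that the no-pain group is not said to determine the effectiveness of the interventions.

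The cost is wording only. Sample size, visits and data collection are unchanged, and Tukey power for 80 kPa rises from 63% to 69% (n = 30) or from 83% to 87% (n = 43).

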#### Provisions for post-trial care {30}

If this study demonstrates the efficacy of any one type of exercise intervention post-treatment and at follow-up with a significant effect size, all participants will be prescribed that intervention to maximize its acceptability and use.

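### The exercise-versus-exercise aim is not carried into the analysis: Tukey runs over five groups, including the non-randomised no-pain group, and the effect size uses an undefined control

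*Protocol article*

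**What the plan says.** All references are to the protocol article.

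- **Aim.** Objectives {7} sets the primary objective: to "determine if different exercise types produce varied outputs on CPM in a subgroup of CLBP patients classified as having CS pain". Trial design {8} adds: "This active treatment concurrent control design will be used to demonstrate superiority of one exercise group over another". Sample size {14} gives its standard deviation for the three exercise groups.
- **Randomisation.** Trial design {8}: "All patients will be allocated in a 1:1:1:1 ratio using random number tables". The four randomised arms are the three exercise groups and patient education alone. The no-pain group is recruited separately.
- **Analysis.** Statistical methods {20a,b} specifies a 5 × 3 mixed design with all five groups as levels of one factor. Tukey's "post hoc analysis will be conducted to establish differences between the groups" then follows, and no pair or subset is marked as primary.
- **Effect size.** The same section obtains it by "dividing the mean difference in outcomes between the intervention and control groups" by their combined SD. It does not say which group is the control.
- **Meaning of control.** Intervention description {11a}: "A group comprising healthy volunteers will serve as the control group". The abstract uses the word in the same way, the five-level factor labels its last level as the no-pain control, and Table 4 sets a single control column against the CLBP column. The comparator section {6b} is broader: "The control group populations comprising the no-pain population and CS-positive patients with CLBP".
- **Use of the result.** Provisions for post-trial care {30} starts: "If this study demonstrates the efficacy of any one type of exercise intervention post-treatment and at follow-up with a significant effect size". In that case all participants are to be prescribed that intervention. No comparator is given.

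**The concern.** The aims point to three comparisons: aerobic versus motor control, aerobic versus strengthening, and motor control versus strengthening. The analysis spreads its error control over 10 pairs, so each of these three must clear a stricter threshold than the stated question requires. Four of the 10 pairs involve volunteers who were never randomised.

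The effect-size sentence is the second problem. If control means the healthy volunteers, as in most places where the article uses the word, the reported effect size mixes any treatment effect with whatever separates people with chronic pain and central sensitisation from people without pain. Randomisation does not protect that contrast. The post-trial care section then attaches a consequence for every participant to a significant effect size, so the ambiguity reaches a stated action.

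**Working it through.** **1. Reproduce the stated power.** Inputs from Sample size {14}: 30 evaluable per group, difference 80 kPa, SD 100 kPa, two-sided alpha 0.05, 30% dropout.

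- Noncentrality: (80/100) / √(2/30) = 0.8 / 0.2582 = 3.098.
- Normal approximation: Φ(3.098 − 1.960) = Φ(1.138) = 0.873.
- Exact t-test with 58 df: 0.861.
- Dropout: 30 / 0.70 = 42.9, so 43 per group. Four arms give 172 patients, and 43 volunteers are added.

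The stated 87% and 43 both reproduce, for a single unadjusted pair.

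**2. Count the pairs in the planned Tukey analysis.** Five groups give 5 × 4 / 2 = 10 pairs: 3 exercise–exercise, 3 exercise–education, 3 exercise–no-pain and 1 education–no-pain.

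**3. Power for one 80 kPa pair under Tukey.** The critical value is q(0.95; k, k(n − 1)) / √2. Power comes from the noncentral t with noncentrality 3.098. The smallest significant difference is the critical value × 100 × √(2/30).

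| Family | Pairs | Critical value | Smallest significant difference | Power | Evaluable n per group for 87% | Recruited at 30% dropout |
|---|---|---|---|---|---|---|
| Three exercise arms | 3 | 2.384 | 61.6 kPa | 76% | 39 | 56 |
| Four randomised arms | 6 | 2.607 | 67.3 kPa | 69% | 44 | 63 |
| All five groups, as written | 10 | 2.762 | 71.3 kPa | 63% | 48 | 69 |

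**4. What each contrast would show.** Simulation of 40,000 trials with 30 per group, SD 100 kPa and five-group Tukey. The true means are assumptions chosen for illustration; the protocol does not give them. Entries are the chance of at least one significant pair of each kind.

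| Assumed true means (kPa) | Exercise–exercise | Exercise–education | Exercise–no-pain |
|---|---|---|---|
| All three exercises +80; education and no-pain 0 | 1.8% | 85.6% | 85.3% |
| All four patient arms +80; no-pain 0 | 1.6% | 1.8% | 85.4% |
| One exercise +80; all others 0 | 78.5% | 63.8% | 63.9% |

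The second row matters for the effect size. No exercise adds anything to education, yet a contrast against the volunteers is significant in 85% of trials, because it reflects the difference between patients and volunteers.

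**5. Side by side on control.** The abstract, the intervention description, the label of the fifth factor level and Table 4 all give the term to the no-pain group. The comparator section includes CLBP patients as well. None of these places gives the name to patient education alone, which is the only randomised non-exercise arm.

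**The case against.** **The plan does state a contrast.** A reader might infer that the deciding comparison is never named. The documents do not support that: the objectives, the trial design and the SD in the sample size all point to exercise versus exercise. The defect is that the analysis section does not carry this aim through.

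**Different results for different contrasts are not in themselves an error.** A reader might take the simulation to show that the same data give opposite conclusions. In the first row above, exercises truly beat education and truly do not differ from each other; 85.6% and 1.8% are correct answers to two questions. The gap follows from the assumed means, and it is significant against not significant, not a reversed direction.

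**There is no alpha inflation here.** Tukey controls family-wise error over all 10 pairs for CPM at one time point, so picking among them afterwards does not raise that error rate.

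**The calculation is simpler than the plan.** The plan is a repeated-measures mixed design; the figures above use one time point, with no baseline and no within-person correlation. They show the relative cost of a wider family and are not the trial's actual power.

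**Some detail belongs in an analysis plan that is not shown.** This is fair for testing order and the labelling of families. It does not cover what the article itself states: the five-level factor, Tukey between those groups, and an effect size against a term used in two ways.

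**Control may mean education.** The trial design speaks of another no-pain control group, which allows education to be a control already. The effect size is a descriptive formula, and the post-trial care section is not the trial's formal decision rule. No section makes exercise versus no-pain the success criterion. That leaves an ambiguity to remove, not proof that the wrong contrast will be used.

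**Conclusion.** The point holds as a mismatch between aim and analysis, and should be fixed. As written, the Tukey family costs about 13 percentage points of power for an exercise pair against a family limited to the three exercise arms (63% against 76%). Both fall short of the stated 87%, which belongs to one unadjusted t-test. These figures rest on the protocol's own 80 kPa, SD 100 kPa and 30 evaluable per group, and on a single-time-point comparison.

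The effect-size definition, on the article's main use of control, can produce a non-randomised contrast that is not a treatment effect. How large that distortion would be cannot be derived from the protocol, which gives no expected difference between patients and volunteers; the 85% above assumes 80 kPa.

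**What to change.** 1. In Statistical methods {20a,b}, name the three exercise pairs (AE–MCE, AE–SS, MCE–SS) on CPM at week 12 as the primary family, with Tukey over those three arms.
2. Report exercise versus patient education as a separate, labelled secondary family of three Dunnett comparisons. Do not gate it on the primary family. If all exercises work equally, the three-pair primary family is significant in only about 5% of trials, so strict gatekeeping would block the education contrasts about 95% of the time.
3. In the effect-size sentence, replace the control group with patient education alone (group 4).
4. Report the no-pain group as a descriptive reference, outside the treatment comparison.
5. In Sample size {14}, restate the power for the adjusted test (about 76% at 30 evaluable per group).
6. Reconcile the efficacy wording in Provisions for post-trial care {30} with the named contrasts.

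The cost is wording only, with no new data or patients. The remaining pairwise comparisons become secondary or descriptive, and the stated power is lower. Keeping 87% under the three-arm Tukey would instead need 39 evaluable, or 56 recruited, per group in place of 43.

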#### Relevant concomitant care permitted or prohibited during the trial {11d}

Any type of concomitant or confounding care and interventions that may influence the study outcomes will not be permitted. However, massage will be administered to the participants who develop muscle soreness after exercises. The participants will be treated with compressive garments if they complain of perceived fatigue after exercise interventions [39]. If the participants are anticipated to need an analgesic or other physiotherapy interventions during the intervention phase, they will be considered ineligible and excluded from the study.

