### Sample size {14}

The sample size was calculated based on the inhibitory effect of the CPT on the PPT, assuming a standard deviation of 100 kPa for the inhibitory effect across all three exercise groups. A sample size of 30 participants per group provides 87% power for an independent *t*-test at a 2-sided alpha of 0.05 to detect a difference in inhibition of 80 kPa [17] when assuming a minimum difference of 0.47 (equivalent to 10% change) as clinically relevant for the CPM effect [55]. Therefore, anticipating a 30% dropout rate, 43 participants will be recruited for each group.

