#### Methods for handling protocol non-adherence and statistical methods for handling missing data {20c}

The research team will undertake all measures to minimize missing of data, and reasons for missing data, if any, will be ascertained using sensitivity analyses. Likelihood-based methods will be used if these reasons are rational. If the data are found to not miss at random, selection models and pattern-mixture models will be used. The *intent-to-treat* analysis will be used to evaluate our objectives based on the groups to which the participants are originally assigned after data transformation was performed.

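### CPM, the primary outcome, is assigned a per-protocol analysis in one section and an intention-to-treat analysis in another, and nothing says which decides the superiority comparison

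*Protocol article*

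**What the plan says.** Four parts of the protocol article bear on who is analysed.

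- Statistical methods {20a,b}: "The primary outcome will undergo a per-protocol analysis".
- Non-adherence and missing data {20c}: the intention-to-treat "analysis will be used to evaluate our objectives based on the groups to which the participants are originally assigned". The same section names likelihood-based methods for missing data, and selection and pattern-mixture models if data are not missing at random.
- Objectives {7}: "The primary objective of the present study is to determine if different exercise types produce varied outputs on CPM". Trial design {8} gives the type of claim: "This active treatment concurrent control design will be used to demonstrate superiority of one exercise group over another".
- Concomitant care {11d}: of participants expected to need an analgesic or other physiotherapy, it says "they will be considered ineligible and excluded from the study".

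The sample size section {14} anticipates 30% dropout and so raises 30 per group to 43. With four randomised arms this gives 172 patients.

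**The concern.** The sentence in {20c} refers to the trial's objectives without restriction, and the first of these is the CPM comparison. CPM is also the primary outcome to which {20a,b} gives a per-protocol analysis. The same comparison therefore has two analysis populations, and neither is called primary or supportive.

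Two things are at stake. First, if the two results differ, the plan does not say which one counts, so the choice can be made with the results in view. That problem needs no assumption about dropout. Second, if the per-protocol sentence governs, the superiority conclusion depends on who stayed and adhered. Adherence can plausibly differ between treadmill walking, strengthening, motor control exercise and education alone. Reasons for stopping, such as pain or soreness, may be related to the outcome.

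**Working it through.** **Comparing the texts.**
1. {20a,b}: primary outcome, per-protocol.
2. {20c}: objectives, intention to treat by original assignment.
3. {7}: the primary objective is the CPM comparison, so the statement in {20c} covers it.
4. Neither section refers to the other, and no other section ranks them. Both are current text.

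**The plan's own figures, from {14}.** SD 100 kPa, difference 80 kPa, 30 per group, two-sided alpha 0.05.
- SE = 100 × √(2/30) = 25.8 kPa.
- Normal approximation: power = Φ(80/25.8 − 1.96) = 87.3%. The exact t-test gives 86.1%. The stated 87% reproduces.
- 30/0.70 = 42.9, rounded up to 43. 4 × 43 = 172.
- 43 × 0.30 = 12.9, so about 13 per arm are expected to drop out. 43 × 0.70 = 30.1, so the stated power already rests on about 30 of 43.

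The sample size arithmetic is sound. The point concerns only the analysis population.

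**Illustration of selective loss.** Assumptions, none of them from the documents: no true effect; 30% lost in each of two arms; in one arm, those lost have the lowest values of a tendency to stay that correlates r with the outcome; in the other arm, loss is unrelated to outcome; SD among those retained is kept at 100 kPa.
- Bias = SD × r × φ(z)/0.70, where z is the 70th percentile of the normal distribution. φ(z)/0.70 = 0.497, so bias = 49.7 × r kPa.
- Rejection rate = Φ(bias/25.8 − 1.96) + Φ(−bias/25.8 − 1.96).

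| Scenario | Bias (kPa) | Rejection at nominal 5% |
|---|---|---|
| Similar loss in both arms | 0 | 5% |
| One arm selective, r = 0.3 | 14.9 | 8.9% |
| One arm selective, r = 0.5 | 24.8 | 16.1% |

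Cross-check: if those lost in one arm average x kPa below those retained, bias = 0.30 × x. x = 50 gives 15 kPa (8.8% by the t-test) and x = 80 gives 24 kPa (15.0%). Against the design difference of 80 kPa, 14.9 and 24.8 kPa are 19% and 31%.

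**Effect of intention to treat on power.** With outcomes on all 43 per arm, the t-test has 95.6% power if the full 80 kPa holds. If 30% of an arm is assumed to gain nothing, the difference is 0.70 × 80 = 56 kPa and power is 72.8%.

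**The case against.** The strongest defence is that the two sentences can coexist. {20c} never calls intention to treat primary, it sits under the non-adherence heading, and reporting both populations is ordinary practice. This is right to the extent that the defect is the missing ranking and not the presence of two analyses. It does not resolve the point. {20c} does not limit itself to secondary objectives, and even if per-protocol was meant for the primary outcome only, the superiority claim would still rest on a subset formed after randomisation. Nor is this detail that can simply be left to a statistical analysis plan, since the article itself fixes two populations for one comparison.

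Three further objections stand and limit the point.

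- A reader might infer that per-protocol analysis would remove 13 of 43 per arm. The documents do not say so: 30% is anticipated dropout, and the per-protocol exclusion could be larger or smaller.
- A reader might infer that the 15 to 25 kPa bias is the price of per-protocol over intention to treat. It is not. Patients lost before the 3-month visit have no outcome under either label, so an intention-to-treat analysis of observed data alone would carry the same bias. The gain depends on continued follow-up and on the methods that {20c} already names.
- A reader might infer from {11d} that patients who need analgesics are removed after randomisation, and that these are the poor responders. The wording speaks of anticipated need and of ineligibility, which could describe screening. The section heading and the mention of the intervention phase point the other way. The text does not settle it.

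It is also tempting to set the bias against the clinically relevant difference of 0.47 in {14}. That figure has no unit there, and no probe area is given, so the comparison is not supported.

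**Conclusion.** The point holds as a conflict between {20a,b} and {20c} and should be corrected before any outcome data are analysed. The population for the confirmatory CPM comparison is undetermined, and the only sentence that names the primary outcome picks the population that does not preserve the randomised comparison.

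The size of the consequence cannot be derived from the documents. The range of 0 to about 25 kPa (5% to 16% rejection) describes informative loss under assumed correlations. Its upper part requires that loss be selective in one arm only. The undetermined choice between analyses rests on the text alone. The wording in {11d} is a secondary ambiguity, and the main conclusion does not depend on it.

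**What to change.** - In {20a,b}, replace the per-protocol sentence with a statement that the primary outcome is analysed in all randomised participants as allocated, using the likelihood-based methods named in {20c}, with the selection and pattern-mixture models as sensitivity analyses. Label the per-protocol analysis supportive.
- Align {20c} so that it names the same primary population.
- In {11d}, state whether the exclusion applies at screening or after randomisation. Which clinical rule applies is for the investigators to decide. Whatever it is, anyone already randomised should stay in outcome follow-up and in the primary analysis as far as consent allows.

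The cost is a short amendment, which under {11b} needs the agreement of both institutions' review boards. The 3- and 6-month assessments are already scheduled, but the documents do not say that participants who stop treatment will attend them, so keeping them in follow-up takes some effort. Non-adherent participants will also dilute the effect somewhat, as the 72.8% power figure illustrates.
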